**Methods:**

A two-arm parallel group, type II hybrid, cluster-randomized control trial design has been implemented to conduct the study between 1 September 2022 and 29 February 2024. Six woredas/districts have been assigned to the intervention arm and the other six to the control arm. Baseline and end-line data have been collected from 120 eligible health management staff (from both intervention arm and control arm). In the intervention arm, district health management staff have been given specialized training and continuous technical assistance as a package called the DIPH strategy by embedding it with the district's current decision-making platform such as Performance Review Team meetings. The DIPH strategy has mainly focused on five-step approaches such as situational assessment, stakeholder engagement, defining/setting priorities, planning, and follow-up. Health management staff in the control arm have performed their regular daily activities. The *χ*^2^ and *t*-tests have been used to check the effect of the intervention. In addition, difference-in-differences estimates have been calculated because the change may inherently occur over time. A *P*-value of <0.05 and a 95% confidence interval have been used to declare the significance of the intervention.

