### Determination of sample size

2.5.

The sample size estimation for the required number of woredas per study arm is based on the statistical formula recommended by Hayes and Bennett (29), assuming 80% power and at least 25 percentage point difference in the performance of data use and maternal healthcare services.$$c=1+(z_{\alpha /2}+z_{\beta }{)}^{2}\frac{\pi_{0}(1-\pi_{0})/m+\pi_{1}(1-\pi_{1})/m+(k_{0}^{2}\pi_{0}^{2}+k_{1}^{2}\pi_{1}^{2})}{{\left(\pi_{0}-\pi_{1}\right)}^{2}}$$where *C* is the number of clusters required (woredas), *Z_α_*_/2_ is the confidence level (95%), Z*_β_* is required power (80%), π_0_ is the true proportion in the absence of intervention (50%), π_1_ is the true proportion in the presence of intervention (75%), *m* implies the individuals sampled in each cluster/woreda (10), *k*_0_ is the coefficient–variation of true proportion in the absence of intervention (0.096942), and *k*_1_ is the coefficient–variation of true proportion in the presence of intervention (0.096942).

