### Data management

2.12.

The data already collected have been routinely checked for completeness and consistency. After appropriate cleaning and coding, the data have been entered into EpiData version 4.6 and exported to SPSS version 23 software for analysis. Descriptive statistics have been generated and presented in narrative, figurative, and tabular forms. The *χ*^2^ and *t*-tests have been used in checking the statistical significance of the intervention and the difference in data use in decision-making and utilization of maternal healthcare services within and between groups. We have employed difference-in-differences estimates because the change may inherently happen over time. Therefore, a control group has captured this intrinsic temporal change without DIPH intervention and subtracted it from the change brought by the DIPH intervention to assess the net effect on key study outcomes. We have calculated the absolute differences in percentages from the baseline and the end line, then calculated the net effect by subtracting the absolute DIPH intervention difference from the control. A *P*-value of <0.05 and 95% confidence interval (CI) have been used to declare the significance of the intervention.

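### Section 2.12 defines the net effect in two opposite directions and ties no test or confidence interval to it, so a within-arm before-after P-value could be used to declare an effect

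*Protocol article*

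**What the plan says.** All the relevant text is in section 2.12 (Data management) of the protocol article and in the Methods paragraph of its abstract.

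- **Direction, first sentence.** The control group captures change that would occur without DIPH, and the analysts "subtracted it from the change brought by the DIPH intervention to assess the net effect on key study outcomes". That is DIPH change minus control change.
- **Direction, next sentence.** Baseline-to-end-line differences in percentages are taken, and the analysts "then calculated the net effect by subtracting the absolute DIPH intervention difference from the control". Read literally, that is control change minus DIPH change.
- **Tests.** The tests named are chi-square and t. Of these, section 2.12 writes: "tests have been used in checking the statistical significance of the intervention and the difference in data use in decision-making". The same sentence goes on to cover the maternal service outcome, and it applies the tests both inside each arm and across the two arms. The abstract says that these "tests have been used to check the effect of the intervention". As a further step it reports that "difference-in-differences estimates have been calculated because the change may inherently occur over time".
- **Decision rule.** Section 2.12 closes with a P-"value of <0.05 and 95% confidence interval (CI) have been used to declare the significance of the intervention". It does not say which contrast the P-value and interval belong to.

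**The concern.** There are two defects in what the text fixes.

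First, adjacent sentences give opposite formulas for the same quantity. An analyst who follows the second would report an improvement as a negative number.

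Second, the net effect is described only as a subtraction of percentages. The tests that decide significance are listed separately and include within-group tests. A within-group before-after test in the DIPH arm measures the intervention effect plus whatever would have happened anyway. The article recognises the problem: the Introduction justifies a comparison group by the need to separate secular trends from real impact, and section 2.12 gives the same reason for using difference-in-differences. Yet nothing in the decision rule stops a significant within-arm P-value from being reported as an effect of DIPH. Section 2.14 makes scale-up depend on effectiveness having been shown, so it matters which P-value settles that question.

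**Working it through.** The article reports no net effect or P-value to reproduce. The check therefore covers the arithmetic of the two sentences and the behaviour of the named tests.

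**1. Direction.** Inputs from section 2.5: 50% without intervention, 75% with it. The control change is not given, so I take 0, 5 and 10 points as assumptions. The DIPH change is 75 - 50 = 25 points.

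| Control change (assumed) | DIPH minus control | Control minus DIPH |
|---|---|---|
| 0 | 25 - 0 = +25 | 0 - 25 = -25 |
| 5 | 25 - 5 = +20 | 5 - 25 = -20 |
| 10 | 25 - 10 = +15 | 10 - 25 = -15 |

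The size is the same in each row and only the sign changes. A P-value or interval width for this contrast would not change either.

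**2. Which contrast the P-value tests.** Inputs: 60 staff per arm per survey (section 2.5) and assumed proportions. Clustering and pairing of staff are ignored, so these P-values only illustrate how the contrasts differ.

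- Two-proportion test: z = (p2 - p1) / sqrt[pbar(1 - pbar) × 2/60], where pbar is the mean of p1 and p2.
- Difference-in-differences (DiD): z = DiD / sqrt[sum of p(1 - p)/60 over the four arm-by-time cells].

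*Both arms 50% to 70%.* Within DIPH, pbar = 0.60, SE = sqrt(0.24 × 2/60) = 0.0894, z = 0.20/0.0894 = 2.24, P = 0.025. End-line between arms: difference 0, P = 1.0. DiD = 20 - 20 = 0. The within-arm test is significant although there is no net effect.

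*DIPH 50% to 75%, control 50% to 55%.* Within DIPH, pbar = 0.625, SE = 0.0884, z = 2.83, P = 0.005. End-line between arms, pbar = 0.65, SE = 0.0871, z = 0.20/0.0871 = 2.30, P = 0.022. DiD = 25 - 5 = 20 points, SE = sqrt[(0.25 + 0.1875 + 0.25 + 0.2475)/60] = 0.1248, z = 1.60, P = 0.11. Three contrasts that the text would allow give three different P-values from the same data.

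*DIPH 60% to 75%, control 40% to 55%.* End-line between arms: P = 0.022. DiD = 15 - 15 = 0. Here the two between-arm contrasts disagree because of a baseline difference. Under randomisation that does not invalidate the end-line test, but it shows why the deciding contrast must be named.

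**3. Power of the candidate estimators (illustrative only).** Inputs from section 2.5: m = 10, k = 0.096942, six woredas per arm, 25-point difference. End-line variance per pair of woredas (one in each arm) = 0.25/10 + 0.1875/10 + 0.096942² × (0.25 + 0.5625) = 0.0514. With woreda effects assumed to persist and staff answers uncorrelated over time, the raw DiD variance is 0.0943, a ratio of 1.84. The correlations below are assumed; power is from the noncentral t distribution, two-sided 5%, with woredas treated as unmatched.

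| Staff correlation over time | Raw DiD (10 df) | End-line adjusted for baseline (9 df) | Plain end-line (10 df) |
|---|---|---|---|
| 0 | 44% | 68% | 68% |
| 0.3 | 57% | 74% | 68% |
| 0.5 | 72% | 82% | 68% |

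If six matched pairs are kept with the same variances, the degrees of freedom fall to 5 (DiD) and 4 (adjusted). Power at correlation 0 is then about 37% and 54%.

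**The case against.** *The reversed sentence is only a slip.* Probably so. The sentence before it states the conventional direction together with its reason. A reader might infer that the plan's net-effect rule is reversed and that the reported result will have the wrong sign. The text does not support that, because it states both directions. What stands is a contradiction to be reconciled.

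*The named tests may already cover the net effect.* A between-group t-test of changes would test the difference-in-differences directly, and the text does not exclude it. An end-line between-arm test is also a valid randomised contrast, and it is the one the sample size is built on. It would therefore be too strong to say that none of the listed tests addresses the intervention effect, or that the P-value certainly belongs to another quantity. What stands is that the text does not choose, and that it lists within-group tests among those used to judge the intervention. Section 2.13 also says that the questionnaire is anonymous, so on its face individual change scores may not be available.

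*Details belong in a fuller plan.* The exact model and standard error may well be left to one. But the article itself fixes the two formulas, the list of tests and the decision rule, and it is these that conflict or leave the door open.

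*Raw difference-in-differences wastes power.* A reader might infer this from the table above. It does not hold as a general finding. The figures rest on assumed correlations and ignore the matching in section 2.6. They need not apply to maternal service utilization, which is a reported percentage over ten indicators. At correlation 0.5 the DiD variance is about 0.93 times the end-line variance. Baseline adjustment gains nothing over a plain end-line comparison at correlation 0 (68% for both).

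**Conclusion.** The point holds in two parts.

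- **Direction.** Section 2.12 contradicts itself. With the plan's own 50% and 75% and a flat control arm, the two sentences give +25 and -25 points. The consequence is limited to the sign, and a drafting slip is the likely cause.
- **Inference.** This is the substantive part. Significance of the intervention is not attached to the net effect, and within-arm tests are among those that could supply it. Under the stated simplifications, a common rise from 50% to 70% gives a within-DIPH P-value of 0.025 with a difference-in-differences of zero. The text permits this outcome; it does not say that the analysts will use the within-arm test.

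The power figures do not carry this conclusion; they bear only on which between-arm analysis to prefer. Whether six woredas per arm is enough is a separate question and adds nothing to the weight of this one.

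**What to change.** Replace the relevant sentences of section 2.12, and align the abstract, so that they state:

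1. Net effect = (DIPH end-line - DIPH baseline) - (control end-line - control baseline), so that a benefit is positive.
2. For each outcome, the primary estimate, 95% CI and P-value come from one between-arm analysis at woreda level: end-line value on arm, adjusted for the woreda's baseline value and taking account of the matched allocation. The raw difference-in-differences is shown as a supporting display.
3. Within-arm before-after tests are descriptive only and cannot be used to declare an effect.

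The cost is a few sentences. No new data are needed, because baseline is already collected in every woreda, and no linkage of individual staff is required. Taking account of the matching leaves fewer degrees of freedom, which should be accepted openly when the model is specified.

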### Ethical consideration

2.13.

An ethical approval letter was obtained from the Institutional Review Board of Dilla University (Ref. No.: duchm/irb/026/2023), and an official letter of cooperation request (Ref. No.: 1000/206/15) was submitted to the respected health facilities. After discussing and explaining the purpose and whole course of the study, written informed consent has been obtained from each health administrative staff member just before the actual data collection. Confidentiality has been assured at all stages of the study by making the questionnaire anonymous. Participant involvement has been voluntary, and those who have been unwilling and needed to quit their participation in the interim have been informed of their right to do so.

### Dissemination plan of the result

2.14.

The findings of the study have been presented to Dilla University and national and international research conferences. The result of the research has been disseminated to the zonal health office and respective health facilities. It has been prepared to be published in a reputable and peer-reviewed journal. This study has been scaled-up if the effectiveness of the intervention is assured.

## Discussion

3.

In low-resource countries such as Ethiopia, the utilization of local data for planning and decision-making health systems is frequently constrained. In addition, despite several government initiatives, maternal health services were not completely utilized. Therefore, this implementation research has been the key priority area in the healthcare system, and it has attempted to standardize possible policy strategies which emanate from multi-level contextual factors. This implementation research has attempted to develop novel insights into how the local government program implements using the established approach. The findings of this study are supposed to give insights into implementation strategies for policymakers and stakeholders to improve data use in decision-making and utilization of maternal healthcare services at the woreda level and to uncover contextual factors that boost the response of these strategies.
